# RT-PCR real time ultrasensitive (“Single copy assay”)

# Residual viremia was measured with an ultrasensitive quantitative real-time RT-PCR (single copy assay), as reported previously by [name] et al (J Clin Microbiol 2003; 41: 4531-6). The optimal HIV-1 RNA detection threshold was 0.3 copies/ml when 5 to 7 ml of starting plasma was available. So we will use this volume from each patient and with a ultracentrifugation step sample concentration. Retrotranscription and amplification will be performed in two steps, so we amplified the study region using a real time quantitative PCR using the primers and fluorescent labels previously described by the authors. The lineal range will be from 1 to 106 copies RNA HIV-1/ml.

**HIV-1 EPISOMAL 2LTR DNA CIRCLES DETECTION**

The presence of HIV-1 episomal 2LTR DNA circles will be detected by qualitative PCR. Enriched 2LTR episomal DNA circles will be extracted selectively from PBMC using QIAprep Spin Miniprep (Qiagen, Valencia, California, USA) following the manufacturer’s protocol for low-copy-number plasmids, as previously described Sharkey et al. [reference 12 ].

A nested PCR flanking the episomal 2LTR DNA circle junction will design. In the first round, 5–20 μL of episomal DNA will amplified in a 50-μL reaction with the following primers: forward, 5’-TAAGATGGGTGGCAAGTGGTCA; and reverse, 5’-TCTACTTGTCCATGCATGGCTT.

The second PCR round was performed using 1 to 2 μL of the first reaction product as the template and primers spanning the unique junction formed by ligation of 5’ and 3’ LTR sequences (forward, 5´-AATCTCTAGCAGTACTGGAAG; reverse, 5´-GCGCTTCAGCAAGCCGAGTCCT). PCR products were analyzed on a 1% agarose gel stained with GelRed (Biotium, Hayward, California, USA).

[figure not shown]

**IMMUNE ACTIVATION AND LYMPHOCYTE SUBSETS ANALYSIS**

Fresh EDTA anticoagulated whole blood will be used to analyze CD4+ and CD8+ T cell activation with the following antibody combination: CD3-allophycocyanin (APC)-Cy7, CD4-peridinin chlorophyll protein complex (PerCP), CD8-phycoerythrin (PE)-Cy7, CD38-phycoerythrin (PE), and HLA-DR-allophycocyanin (APC). Lymphocyte subpopulations will be defined as naïve (CD45RA+CCR7+), T central memory (CD45RA-CCR7+, TCM), T effector memory (CD45RA-CCR7-, TEM), and T effector memory RA+ (CD45RA+CCR7-, TemRA). To analyze lymphocyte subsets this antibody combination we will used: CD3-allophycocyanin (APC)-Cy7, CD4-peridinin chlorophyll protein complex (PerCP), CD8-phycoerythrin (PE)-Cy7, CD45RA- phycoerythrin (PE), and CCR7-allophycocyanin (APC), β7-allophycocyanin (APC). Antibodies will be from Becton Dickinson (Becton Dickinson, NJ, USA), and an unstained control will be performed for all samples. Briefly, 100 µL of blood were lysed with 200 µl of FACS Lysing solution (Becton Dickinson) for 30 min at room temperature, will be incubate with the antibodies during 20 min at 4ºC, wash and resuspend in PBS containing 1% azida. Cells will be analyzed in a Gallios flow cytometer (Beckman-Coulter, CA, USA). At least 15000 CD3+ cells were collected for each sample and analyzed with Kaluza software (Beckman-Coulter) initially gating lymphocytes according to morphological parameters.

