## **Secondary objectives**

1. To quantify in vitro the viral reservoir of these patients throughout the study.

2. To study in vitro the residual viremia using an ultrasensitive PCR assay (Single Copy Assay) and the Episomal 2-LTRs DNA circles detection.

3. To study the immune activation markers as indirect markers of residual viremia

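### As written, the lymphocyte-subset panel in Annex IV carries CCR7 and β7 on the same dye (APC), so CCR7-defined subsets could not be read from a single tube

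*Protocol*

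**What the plan says.** The section of Annex IV on immune activation and lymphocyte subsets describes two stainings on fresh whole blood.

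- **Activation panel.** CD3, CD4 and CD8, followed by "CD38-phycoerythrin (PE), and HLA-DR-allophycocyanin (APC". Each antibody has its own dye.
- **Subset panel.** It is introduced in the singular: "To analyze lymphocyte subsets this antibody combination we will used: CD3-allophycocyanin (APC)-Cy7". CD4-PerCP, CD8-PE-Cy7 and CD45RA-PE follow, and the list closes with "phycoerythrin (PE), and CCR7-allophycocyanin (APC), β7-allophycocyanin (APC".

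The subsets are defined by two markers only: "Lymphocyte subpopulations will be defined as naïve (CD45RA+CCR7+), T central memory (CD45RA-CCR7+, TCM", then "T effector memory (CD45RA-CCR7-, TEM), and T effector memory RA+ (CD45RA+CCR7-, TemRA". β7 enters none of the four definitions. The only control mentioned is that "an unstained control will be performed for all samples". The section describes no second tube, no alternative dye for β7 or CCR7, and no gating rule to tell them apart.

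**The concern.** A cytometer reads dyes, not antibodies. Two antibodies carrying the same dye in one tube give one combined signal, and no gating on that channel can split it afterwards. Here one of the two is CCR7, the marker that separates central from effector memory and naïve from TemRA.

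The direction of the error would be fixed. CCR7-negative cells that carry β7 would move from TEM to TCM, or from TemRA to naïve, never the other way. More cells or more patients would not average this out. In a study that follows each patient over time, a change in β7 expression could also look like a change in memory composition. Because the staining uses fresh blood, samples stained wrongly could not be stained again later.

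**Working it through.** The plan gives no figure to reproduce, so the check is a count followed by an illustration.

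**Step 1: count antibodies against dyes (both lists from Annex IV).**

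| Panel | Antibodies | Distinct dyes | Dye used twice |
|---|---|---|---|
| Activation: CD3 APC-Cy7, CD4 PerCP, CD8 PE-Cy7, CD38 PE, HLA-DR APC | 5 | 5 | none |
| Subsets: CD3 APC-Cy7, CD4 PerCP, CD8 PE-Cy7, CD45RA PE, CCR7 APC, β7 APC | 6 | 5 | APC |

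The clash is confined to the subset panel.

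**Step 2: what one tube would report.** Take CD45RA-negative cells. Let c be the true share that is CCR7-positive (TCM) and b the share of CCR7-negative cells that carry β7. The protocol gives neither, so both are assumptions. Any cell with either marker is taken to read as APC-positive.

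- Apparent TCM share = c + (1 − c)b
- Share of apparent TCM that is truly TEM = (1 − c)b / [c + (1 − c)b]

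| c | b | Apparent TCM | Of which truly TEM |
|---|---|---|---|
| 0.3 | 0.1 | 0.37 | 19% |
| 0.3 | 0.3 | 0.51 | 41% |
| 0.3 | 0.5 | 0.65 | 54% |
| 0.5 | 0.1 | 0.55 | 9% |
| 0.5 | 0.3 | 0.65 | 23% |
| 0.5 | 0.5 | 0.75 | 33% |
| 0.7 | 0.1 | 0.73 | 4% |
| 0.7 | 0.3 | 0.79 | 11% |
| 0.7 | 0.5 | 0.85 | 18% |

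With b = 0 the apparent and true shares agree for every c. The same formula applies to CD45RA-positive cells, with naïve in place of TCM and TemRA in place of TEM.

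**Step 3: change over time.** The bias at a visit is (1 − c)b, so it cancels in a within-patient difference only if that product is the same at both visits.

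- *True composition constant, β7 changing.* With c = 0.5, a rise in b from 0.1 to 0.3 moves apparent TCM from 0.55 to 0.65, although no cell has changed subset.
- *β7 share constant, true composition changing.* The apparent change is (1 − b) times the true one. With b = 0.3, c rising from 0.5 to 0.7 appears as 0.65 to 0.79, which is 0.14 instead of 0.20.

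**Step 4: can the stated control help?** An unstained sample shows background in the APC channel. It cannot say which of two APC antibodies produced a signal above background.

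**Step 5: what depends on the subsets.** Secondary objective 3 reads "To study the immune activation markers as indirect markers of residual viremia", and activation is measured by the CD38/HLA-DR panel, which has no clash. The study plan footnote and the list of laboratory determinations also name activation markers, not memory subsets. The statistical section models only IUPM, the measure of the reservoir. Neither the subsets nor β7 appear in any objective, endpoint, schedule or laboratory list.

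**The case against.** The best defence is that two tubes were meant. The subset list repeats the activation panel's backbone and reaches a natural end at CCR7-APC, introduced by the closing conjunction; β7-APC is then tacked on. That fits a five-colour tube plus a variant with β7 in place of CCR7, compressed into one sentence of a loosely written annex that mixes past and future tenses. If so, the laboratory would do nothing wrong and only the text would need repair. This is plausible and cannot be ruled out. It does not clear the text, which speaks of one combination and mentions no second tube: someone following it literally would stain both together.

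A reader might also infer that secondary objective 3 is compromised, because subsets and activation share a section heading. The documents do not support that: the activation panel has five antibodies on five dyes.

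A reader might look for a definite figure for the misclassified share. None can be given. The protocol states neither a subset distribution nor a β7 frequency, so every number in the illustration follows from assumed inputs.

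**Conclusion.** The defect in the text is certain: one combination, six antibodies, five dyes, with the shared dye on the marker that all four subset definitions need. The consequence is conditional. It requires that CCR7-APC and β7-APC go into the same tube and that some CCR7-negative cells carry β7. Under those conditions TCM and naïve are overstated, TEM and TemRA are understated, and β7 cannot be read.

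Over the assumed ranges c = 0.3 to 0.7 and b = 0.1 to 0.5, the wrongly labelled part of apparent TCM runs from 4% to 54%; it is zero if b = 0. The stronger statement, that every subset percentage in this trial will be wrong, goes beyond the documents, because it takes the one-tube reading and a non-zero b as established.

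Severity is minor. The subsets are an exploratory readout in a pilot of 10 patients and are not tied to any objective. The primary IUPM endpoint is untouched.

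**What to change.** Amend the Annex IV section in one of two ways:

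1. Put β7 on a fluorochrome not otherwise used in the panel, that is, none of PE, PE-Cy7, PerCP, APC and APC-Cy7. The laboratory should confirm that the cytometer has a free detector for it.
2. State that β7-APC is stained in a separate tube without CCR7-APC.

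The options are not equivalent. Only the first allows β7 to be read within the CCR7-defined subsets. The second gives valid subsets and a valid β7 readout, but not the two together on the same cells. The protocol does not say which is wanted, so the choice should follow the intended use of β7.

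In either case, state that the same panel is used at every visit at which subsets are measured. With β7 out of the CCR7 channel, b drops out of the formula and the apparent TCM share equals c.

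The cost is one changed conjugate, or one extra tube of about 100 µL of blood per sample, with no extra visit or staff. If two tubes were already intended, only the wording changes.
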